### The problem

A shortage of transplantable organs is a global problem. Despite Canada’s envied healthcare system and economic status amongst developed nations, we perform very poorly in organ donation. There are two types of organ donation: live donation when a living person donates an organ or part of an organ to another individual and deceased donation when an individual becomes a donor following their death. Deceased donation can occur after neurological determination of death (NDD) or cardiocirculatory (or cardiac) death (DCD). DCD was not used routinely in Canada until 2006. In 2010, the deceased donor rate in Canada was 13.6 per million population (PMP) [1] compared to 32 PMP in Spain and 25 PMP in the United States, with no improvement in the past decade (2001, 13.1 PMP) [1]. While Canada has had 465 to 485 deceased donors yearly over the past five years [1], 4,500 Canadians remain active on transplant waiting lists [2,3].

Use of DCD donors is frequent worldwide and accounts for the largest increments in deceased organ donation. Variations in the use of DCD continue, however, in jurisdictions within Canada and worldwide [2,4]. Since 2006, DCD has grown in some Canadian jurisdictions but has remained stagnant or absent in others. In 2011, DCD accounted for 20% of all deceased organ donors in Ontario (3.1 DCD donors PMP), 9.5% in Quebec (1.6 PMP), 8.7% in BC (1.5 PMP), 8% in Alberta (0.8 PMP), 8% in Nova Scotia (2.1 PMP), and 0% in Saskatchewan, Manitoba, New Brunswick, Prince Edward Island, and Newfoundland [2,5]. Compared to other jurisdictions, even Ontario’s ‘high’ DCD rate is relatively low. The DCD rate in the UK is 5.2 PMP with some regions reporting rates up to 12.3PMP [6]. Canada would see a dramatic increase in the number of available organ donations if DCD donation rates were to increase to international standards. Reasons for the wide international variations in DCD uptake remain unknown.

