### Outcome measures

The primary outcome measure for evaluation of the knowledge translation intervention will be total donation rate (defined as the total number of organ donors, NDD plus DCD combined) per million population (PMP) per six months. Although a change in the DCD rate might seem to be a more appropriate outcome measure, we chose the total donation rate for two reasons. First, there is a concern that increased use of DCD might lead to fewer NDD donors [42]. If our intervention was successful at increasing DCD donors but led to a reduction in NDD donors, this would not be considered a positive intervention that should be adopted. If this occurred, use of the DCD rate alone as the primary outcome could potentially mislead stakeholders that our intervention should be implemented. By using the total donation rate, we will judge our intervention to be successful only if total donors increase. We hypothesize that there will be an increase in the total donation rate that is driven by an increase in the DCD rate with a neutral or even positive effect on the NDD donor rate as has been recently seen in the province of Ontario [43]. Second, since routine use of DCD only resumed in 2006 in Canada, observed DCD counts were all zero until 2005 and too small thereafter (<5 per million) to allow stable analysis of six-month intervals as planned (only seven pre- and three post-intervention time points for analysis). In contrast, the number of time points available for NDD and total donations is at least 30 (24 pre-, six post-intervention). So from a statistical perspective as well, total donation rate is the preferred primary outcome. Secondary outcome measures will be DCD rate (PPM per year) and (NDD) rate (PPM per six months).

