### Analysis plan

The proposed method of analysis is a segmented linear regression autoregressive error model of the observed aggregate outcomes in each of four regions that comprise the 10 Canadian provinces: Atlantic Canada (New Brunswick, Nova Scotia, Prince Edward Island, and Newfoundland), Ontario, Quebec, and Western Canada (British Columbia, Alberta, Saskatchewan, and Manitoba). This approach is commonly used in health services research because it can tolerate fewer time points than autoregressive integrated moving average (ARIMA) models and is amenable to intuitive graphical presentation [41]. The first step of the analysis will be a graphical inspection of donation rates over time, at six-month intervals, in each of the study regions. The full model will be fitted by specifying a pre-intervention intercept and slope, and two parameters that represent the change in intercept and change in slope after introduction of the intervention. Maximum likelihood estimation will be used as it is considered one of the most appropriate methods of estimation for small samples with autocorrelated errors [44]. The analysis will adjust both parameter and variance estimates for autocorrelation. No adjustment for seasonal trends is anticipated.

The significance of the knowledge translation intervention will be evaluated using a likelihood ratio test of the change parameters. The null hypothesis is that both intercept and slope changes are zero; the alternative hypothesis is that at least one of intercept or slope change is non-zero. The immediate and gradual effect of the knowledge translation intervention will be estimated using confidence intervals for both absolute and relative change in the intercept and slope, using methods developed by Zhang *et al.*[45]. The overall effect, combining intercept and trend changes, will be estimated using the absolute and relative difference in the predicted post-intervention outcome versus the predicted outcome from the secular trend (counterfactual estimate) together with confidence intervals, using the methods developed by Zhang *et al.*[45]. As recommended, we will report 95% confidence intervals using the 99% critical value to account for the fact that time series with a small number of time points and large autocorrelation may produce artificially narrow confidence intervals.

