To assess the fit of the final model, we will examine residual plots around the predicted regression lines. The residual plots will be used to check whether the linear assumption for the segmented regression model is satisfied. If the linear assumption is not satisfied, either log-transformation of the outcome or Poisson regression with population size as an offset term will be carried out.

Due to the limitations of our sample size (a minimum of 30 time points) we will conduct sensitivity analyses using methods recently developed for short interrupted time series. First, we will use the double-bootstrap approach developed by McKnight *et al.*[46] who demonstrated that empirical coverage and type I error rates are close to the nominal levels for as few as 20 observation times. Second, we will use the restricted maximum likelihood (REML) approach together with Kenward-Roger degrees of freedom investigated by Forbes *et al.*[47]. They showed that type I error rates of this approach are close to nominal size with as few as 30 observation times. Finally, for the secondary analysis of DCD rates, we anticipate only three available post-intervention observation points (at annual intervals) which is insufficient to reliably estimate a parametric trend after the intervention. Following Bloom [48], we will specify post-intervention time for DCD as a categorical variable (*i.e.*, post-intervention change will be estimated as deviations from the pre-intervention trend in post-intervention years one, two, and three).

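### The only stated remedy for a failed linearity check corrects exponential-type curvature, not a change of trend inside the baseline such as the 2006 resumption of DCD

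*Protocol article*

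**What the plan says.** All references are to the protocol article, Objective three.

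- **Outcome (Outcome measures).** The primary outcome is the "total donation rate (defined as the total number of organ donors, NDD plus DCD combined) per million population (PMP) per six months".
- **Model (Analysis plan).** Each region gets one model, "specifying a pre-intervention intercept and slope, and two parameters that represent the change in intercept and change in slope after introduction of the intervention". No other time term is named. The overall effect is the predicted post-intervention outcome set against the extrapolated secular trend.
- **Check.** "The residual plots will be used to check whether the linear assumption for the segmented regression model is satisfied".
- **Remedy.** "If the linear assumption is not satisfied, either log-transformation of the outcome or Poisson regression with population size as an offset term" is to be carried out. No change point, polynomial or shorter baseline is offered for the primary outcome. Categorical time appears only for the post-intervention years of the secondary DCD analysis, and there too the deviations are taken from a pre-intervention trend.
- **History of the series.** Outcome measures says that "observed DCD counts were all zero until 2005 and too small thereafter (<5 per million". The problem section says: "Since 2006, DCD has grown in some Canadian jurisdictions but has remained stagnant or absent in others".

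**The concern.** The assumption under test is that the rate moves along one straight line in time before the intervention. A log or log-link changes the scale of the outcome and leaves the time function alone. It therefore repairs one shape, growth by a constant percentage, and no other. The shape that the protocol's own history suggests is different: a component of the primary outcome is zero for the first part of the baseline and positive, in some regions growing, for the rest.

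An analyst who sees curvature from that source and follows the rule will log the outcome, regard linearity as dealt with, and extrapolate a line that is still wrong. The reported effect is the distance from that line, so the error passes directly into the estimate.

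**Working it through.** **What can be reproduced.** The protocol gives no figure for this point. Table 3 allows a consistency check: count = 2 × population × rate, so Ontario's population is 17.1/(2 × 0.64) = 13.36 million at r = 0.4 and 25.4/(2 × 0.95) = 13.37 million at r = 0.8. These agree. The detectable slopes cannot be reproduced because the mean square errors are not given.

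**Inputs.** Ontario in 2011 (The problem): DCD 3.1 PMP per year, 20% of donors. Total = 3.1/0.20 = 15.5 and NDD = 12.4 per year. Per six months that is 7.75, 6.2 and DCD 1.55.

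**Assumptions.** The baseline is taken as 2001-2012. This fits 24 half-years and the seven annual DCD points from 2006, but the protocol does not state it. NDD is flat at 6.2. The DCD path is mine. Series are noise-free, the true effect is zero, and six half-years follow.

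**Method.** With separate post-intervention intercept and slope and independent errors, the pre-intervention line depends only on the first 24 points. False effect = true value − extrapolated value, averaged over t = 25 to 30 (mean t = 27.5).

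*Bend in 2006, growth continues* (true post mean 8.67):
- raw line 5.664 + 0.0922t gives 8.20 at t = 27.5, so the false effect is +0.47
- log line exp(1.749 + 0.01325t) gives 8.28, so +0.39

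*Rise from 2006, plateau from 2009* (true post mean 7.75):
- raw line 5.740 + 0.0937t gives 8.32, so −0.57
- log line exp(1.759 + 0.01351t) gives 8.42, so −0.67

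| Shape | Raw | Log | Poisson |
|---|---|---|---|
| 2006 bend, continuing | +0.47 (5.4%) | +0.39 (4.5%) | +0.35 (4.0%) |
| Rise, then plateau | −0.57 (−7.3%) | −0.67 (−8.7%) | −0.69 (−8.9%) |
| Constant-percentage growth, +25% over baseline | +0.06 (0.8%) | 0.00 | 0.00 |
| Constant-percentage growth, +60% over baseline | +0.32 (3.0%) | 0.00 | 0.00 |

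Units are PMP per six months; percentages are of the true post-intervention mean. For the bend, the remedy removes (0.466 − 0.388)/0.466 = 17% (log) or (0.466 − 0.347)/0.466 = 26% (Poisson). For the plateau, it enlarges the error by 0.673/0.566 − 1 = 19% (log) or 0.687/0.566 − 1 = 21% (Poisson).

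**Sensitivity.** At the last half-year, other choices of starting level and path give, raw / log / Poisson, +6.2 to +8.3% / +5.0 to +7.1% / +4.6 to +6.4% for the bend, and −7.4 to −9.4% / −8.9 to −11.0% / −9.0 to −11.1% for the plateau.

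**Why the log does so little.** Between 12.4 and 15.5 PMP per year, a straight line and a log-linear line with the same end points differ by at most 0.09.

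**Effect on the test.** For 80% power the 2-df test needs noncentrality 9.635, so Ontario's 0.64 at r = 0.4 implies a residual SD of 0.64/0.679 = 0.94 or 0.64/0.622 = 1.03, depending on whether the mean square error is the innovation or the marginal variance. The approximate rejection rates at nominal 5% below pair r = 0 with SD 0.94 and r = 0.4 with SD 1.03:
- bend: raw 10.1% (r = 0) and 7.0% (r = 0.4); log 7.1% and 5.8%
- plateau: raw 13.3% and 7.9%; log 13.5% and 8.0%

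**Alternatives, same series.** The counterfactual standard error at t = 30 is √(x′(X′V⁻¹X)⁻¹x), shown relative to the single line for r = 0 and r = 0.4.

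| Pre-intervention time function | Bend | Plateau | Relative SE |
|---|---|---|---|
| One change point, 2006 | 0.00 | −0.84 | 1.38, 1.35 |
| Change points 2006 and 2009 | 0.00 | 0.00 | 2.45, 2.24 |
| Line on 2009-2012 only | 0.00 | 0.00 | 2.72, 2.35 |
| Quadratic | −0.45 | −0.84 | 2.44, 2.29 |

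**The case against.** **The rule is not wrong for every curve.** For constant-percentage growth, log or Poisson removes the false effect completely. A reader might infer that the remedy never works, or that the primary estimate will be biased. Neither follows: the outcome depends on the shape of series that the protocol does not show.

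**The sizes rest on invented series, and Ontario is the least favourable case.** This stands. The 2011 DCD rates elsewhere are lower (Quebec 1.6, British Columbia 1.5, Nova Scotia 2.1, Alberta 0.8 PMP, five provinces at zero), so a bend from this source would usually be smaller. The national rate moved only from 13.1 to 13.6 PMP between 2001 and 2010. It is also tempting to cite the 2011 levels implied by Table 3, about 5.5 to 8.9 PMP per six months, as proof that the log is nearly linear here. That is a spread between regions, not a range over time, and the argument above does not use it.

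**A more flexible time function has its own risks.** This also stands. A single 2006 change point worsens the plateau case, and a quadratic fails in both cases at more than twice the standard error. The fix must match the visible shape.

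**The trigger is weak under any wording.** Even a formal 5% test for a 2006 change point has low power. With SD 0.94 and r = 0, the noncentrality is 1.255/0.94² = 1.42 for the bend (power about 21%) and (1.478 − 1.039)/0.94² = 0.50 for the plateau (about 10%). Residual plots will often miss a modest bend.

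**Such details belong in the analysis plan document.** This would be decisive if the article were silent. It is not: it names the remedy, and the remedy fits one kind of curvature only.

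**Conclusion.** The point holds in a limited form. The stated remedy addresses exponential-type curvature and leaves a within-baseline change of trend largely uncorrected. In Ontario-like series with no effect, the false effect averages about 4-5% of the rate after the remedy for a continuing bend (5.4% before), and about −9% for a rise then plateau (−7.3% before). The direction depends on the shape.

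The harm is mainly to the effect estimate. A reader might infer serious inflation of the type I error. The calculation gives only a modest excess, and for the bend the log lowers it. For scale, if Ontario's detectable slope of 0.64 is a change per half-year, counted from one at the first post-intervention point, it averages 0.64 × 3.5 = 2.24 PMP over six points, well above the false effects of 0.35 to 0.69.

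The conclusion rests on the assumed baseline years, flat NDD, the DCD paths and, for the test, the back-solved SD. The change is worth making because the cause is known in advance and the plan's rule directs the analyst to a remedy that does not act on it.

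**What to change.** Replace the remedy sentence in the Objective three analysis plan with a rule along these lines:

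- If pre-intervention residuals show a bend or level change, change the pre-intervention time function to match the visible shape: a pre-specified change point at the 2006 DCD resumption, with a second change point or a recent-baseline fit if the trend then levels off.
- Keep the autoregressive errors, and report this fit beside the single-line result.
- Keep log-transformation or Poisson for proportional growth, or for residual spread that rises with the level.
- Do not offer a quadratic. Extrapolated to the last half-year, it multiplies the counterfactual standard error by about 2.3-2.4 and does not follow either shape examined.

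**Cost.** The change is a few lines of wording. One change point widens the counterfactual standard error about 1.4 times. A second one, or a line on the last four years only, costs about 2.2 to 2.7 times, so it should be used only where levelling off is visible. Because residual plots on 24 points will often miss a modest bend, the 2006 change-point fit could also be reported as a sensitivity analysis in every region whatever the plots show.

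### The regional DCD analysis applies maximum likelihood to ten annual points: its 95% intervals under-cover unless two unstated corrections are both made, and a likelihood ratio test over-rejects either way

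*Protocol article*

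**What the plan says.** The general method is set out in the protocol article under Objective three, Analysis plan: a "segmented linear regression autoregressive error model of the observed aggregate outcomes in each of four regions". On estimation it says "Maximum likelihood estimation will be used", and on intervals "we will report 95% confidence intervals using the 99% critical value". The change parameters are to be tested with a likelihood ratio test.

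For DCD, Outcome measures defines an annual rate, "Secondary outcome measures will be DCD rate (PPM per year", and gives the length of the series as "only seven pre- and three post-intervention time points for analysis". The Analysis plan repeats that "we anticipate only three available post-intervention observation points (at annual intervals", which it regards as too few for a fitted post-intervention trend. It therefore codes the post-intervention years as categories: "post-intervention change will be estimated as deviations from the pre-intervention trend in post-intervention years one, two, and three". No other estimator, interval rule or test is named for DCD.

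Two small-sample sensitivity methods are planned because the main series may have only 30 points. By the article's own account, the double bootstrap performs close to nominal from 20 observation times, and REML with Kenward-Roger degrees of freedom from 30.

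**The concern.** Three of the five mean parameters are year indicators, and each one fits its own post-intervention point exactly. The autocorrelation and the residual variance therefore rest on seven pre-intervention points around a fitted line. ML makes no allowance for this. Its variance estimate divides by 10 although only 5 residual degrees of freedom remain, and its autocorrelation estimate is strongly biased downwards in so short a series. Using the 99% critical value is meant to offset intervals that are too narrow, but it may not be enough at this length. Neither sensitivity method is cited as adequate at ten points.

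DCD is secondary, but it matters for interpretation. The article hypothesises that any rise in total donation will come from DCD, and this analysis is where that mechanism would be seen, in four regions and three years each. If the intervals are too short and the test too liberal, random variation will often be reported as a change in DCD.

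**Working it through.** **Inputs.** From Outcome measures: 7 pre + 3 post = 10 annual points. From the Analysis plan: 5 mean parameters (intercept, slope, three yearly deviations), ML, the 99% critical value, regional series. From Power calculations: r = 0.1 to 0.5 is described as plausible, and 0.4 and 0.8 are used there for the primary outcome. No r is given for DCD, so 0 to 0.5 is an assumed range, with 0.8 as an extreme. The article gives no coverage or power figure for DCD; the only figure to test is the nominal 95%.

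**Step 1: exact check with independent errors and no autocorrelation estimated.**
- Residual degrees of freedom: 10 − 5 = 5.
- Divisor 5 with 2.576: P(|t₅| < 2.576) = 95.0%. At this length the normal 99% value only restores what an ordinary t interval would give, and leaves nothing in reserve for autocorrelation.
- ML divisor 10: the standard error shrinks by √(5/10), so coverage is P(|t₅| < 2.576/√2) = P(|t₅| < 1.82) = 87.2%.

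**Step 2: simulation with r estimated.** 50,000 Gaussian AR(1) series of length 10 per setting, no true effect, r profiled by exact ML. Coverage (%) for years 1/2/3:

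| Variance divisor | Critical value | r = 0 | r = 0.4 | r = 0.5 |
|---|---|---|---|---|
| 10 (ML) | 2.576 (normal) | 78.1/79.2/80.5 | 75.5/72.9/71.5 | 75.1/71.2/68.7 |
| 5 | 2.576 (normal) | 89.1/89.7/90.9 | 87.2/85.3/84.3 | 87.0/84.0/82.0 |
| 10 (ML) | 4.032 (t₅) | 91.4/92.0/93.0 | 89.8/88.2/87.5 | 89.6/86.9/85.4 |
| 5 | 4.032 (t₅) | 96.8/97.0/97.6 | 96.0/95.0/94.8 | 95.8/94.2/93.7 |

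The mean ML estimate of r is −0.38 when the true value is 0 and −0.23 when it is 0.4. At r = 0.8 the first row falls to 72.8/66.0/61.3. Independent Poisson counts with means from 3 to 40 give 78% to 81% for the first row, so the result does not depend on normal data.

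**Step 3: likelihood ratio test.** Carried over to DCD, the planned test compares the five-parameter model with the two-parameter trend (chi-square, 3 degrees of freedom, 5% level). Type I error is 33% at r = 0, 37% at r = 0.4 and 38% at r = 0.5. Neither the variance divisor nor the choice between z and t enters this test.

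**Step 4: an alternative.** REML with the t₅ 99% value (4.032) covers about 95% to 98% for r = 0 to 0.5, and 96.8/94.7/93.3 at r = 0.8. REML with 2.576 covers only 89% to 93% for r = 0 to 0.4.

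**Step 5: the smallest region.** Table 3 implies about 5.9/0.14 = 42 deceased donors in Atlantic Canada in 2011. For that year the Background gives "8% in Nova Scotia (2.1 PMP), and 0% in Saskatchewan, Manitoba, New Brunswick, Prince Edward Island, and Newfoundland". Nova Scotia cannot have had more than the regional 42, so Atlantic DCD donors were at most 0.08 × 42 = 3.4, that is, about 3.

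**The case against.** The strongest reply is that the article does not fix the details on which the low figure depends. It names no variance divisor and does not say whether the 99% value is normal or t. With divisor 5 and t₅ the same text gives near-nominal coverage. Such details are often left to a fuller document. ML is also not restated for DCD, whose coding follows a separate cited source. This stands as a limit on the claim: a reader might infer that the DCD intervals will cover only 71% to 81%, and the article supports that only for the ML variance with the normal value. It does not remove the point. Divisor n is what ML gives, either correction alone falls short, and the likelihood ratio test is affected under every reading in which it is applied to DCD.

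The article also openly acknowledges the short DCD series, makes DCD secondary for that reason among others, and plans a log transformation or a Poisson model with a population offset. That fallback is real, but it is triggered by non-linearity in residual plots, not by small counts or few degrees of freedom.

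Two further inferences should be resisted. The bound of about 3 Atlantic donors is for 2011 only; it does not describe the whole series, least of all the years in which the intervention aims to raise DCD. Nor is the study's main conclusion at risk: the intervention is judged on total donors, and that series and its power calculation are untouched.

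**Conclusion.** The point holds in conditional form. The article implies ten annual points and five mean parameters per region for DCD, analysed by ML. With the ML variance and 2.576, coverage of the yearly deviations is about 71% to 81% for r = 0 to 0.4, and 69% to 75% at r = 0.5. With one of the two corrections it is 84% to 93% for r = 0 to 0.4; with both it is about 95% to 98%. The likelihood ratio test, if extended to the three deviations, has a type I error of about 33% to 37% over r = 0 to 0.4 instead of 5%.

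These figures assume AR(1) errors, no true effect, and that the general method carries over to DCD because nothing replaces it. The range of r is assumed, but under-coverage is already clear at r = 0. The effect is confined to a secondary outcome, though one that is central to explaining the primary result.

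**What to change.** For the DCD analysis, replace ML, the likelihood ratio test and the normal critical value with REML (variance on residual degrees of freedom) and intervals using the 99% critical value of t on 5 degrees of freedom. State the divisor and the reference distribution, and drop the DCD likelihood ratio test. Report regions with very few DCD donors, such as Atlantic Canada, descriptively.

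The change is to analysis wording only. The price is precision: at the same estimated r, intervals become √2 × 4.032/2.576 = 2.2 times as wide as with the ML variance and 2.576, and REML's different estimate of r will alter that ratio somewhat. That width reflects what ten points can show.

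A pooled national count series may be added as a supplement if it allows for autocorrelation, but it should not replace the regional analysis. A six-month national series would run against the article's own reason for using annual DCD data and would give up regional inference. It would not be safe without an autocorrelation term either. An overdispersed Poisson model of 14 + 6 half-years, with an assumed mean rising to 30 per half-year by 2011, covered about 95% with independent counts but only 84% to 88% at r = 0.4.
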